## Abstract

**Background:**

Continuous anticoagulation based on the CHA2DS2‐VASc score is recommended to prevent embolism caused by atrial fibrillation (AF), but it does not consider AF episodes. The Apple Watch's continuous heart rhythm monitoring and fast‐acting direct oral anticoagulants (DOACs) could enable precise, episode‐tailored anticoagulation, reducing bleeding risks while preventing stroke. This study evaluates Apple Watch‐guided personalized anticoagulation therapy, adjusting DOAC usage based on real‐time AF detection.

**Methods:**

This multicenter prospective single‐arm study will enroll patients who have maintained sinus rhythm post‐ablation and are on DOACs. The target enrollment is 50 patients free of AF for at least 30 days following the initiation of Apple Watch monitoring. If no AF occurs for the first 30 days of monitoring, anticoagulants will be discontinued on day 31. If AF is confirmed after day 31, DOAC administration will be resumed and continued until the end of the observation period. The primary endpoint is the reduction in the total number of days with DOACs from day 31 to day 360 compared to the conventional method of continuing anticoagulation. Secondary endpoints include all‐cause mortality, stroke, systemic thromboembolism, bleeding events, and Apple Watch malfunctions.

**Results:**

Enrollment of a total of 50 patients was completed in April 2024. Follow‐up of the last enrolled patient will be completed in April 2025 and primary results are expected to be available in late 2025.

**Conclusions:**

The Up to AF trial is the first trial to evaluate Apple Watch‐guided personalized anticoagulation therapy. This trial represents a potential advancement in personalized medicine for AF management.

## INTRODUCTION

1

More than 33 million individuals globally are afflicted by atrial fibrillation (AF) [1], with an estimated incidence of exceeding 10% in those over the age of 70 [2]. Numerous complications are associated with AF, including stroke, which can significantly impact prognosis. The effective management of AF is a pressing issue in an aging society. To prevent embolism caused by AF, anticoagulant therapy is performed based on the CHA_2_DS_2_‐VASc score, which is a risk assessment tool for cerebrovascular events in AF patients [3]. The long‐term continuation of post‐ablation anticoagulation therapy is recommended to be guided by the patient's stroke risk profile, without considering AF burden [4]. This approach is necessitated by the often brief and asymptomatic nature of AF episodes, making timely recognition and intervention challenging.

Advances in devices capable of continuous heartbeat monitoring have demonstrated that embolic risk varies with AF burden [5]. As continuous anticoagulation increases bleeding events [6], it may be detrimental with minimal benefit for those with no or minimal AF burden. Traditionally, anticoagulant therapy involves the use of warfarin, which requires weeks to achieve therapeutic anticoagulant effects. However, the recent introduction of direct oral anticoagulants (DOACs) allows for the rapid attainment of anticoagulant effects within hours of oral administration. Consequently, while warfarin must be administered even in the absence of AF to maintain therapeutic blood concentrations for when AF occurs, DOACs can be administered upon the onset of AF.

Studies utilizing implantable cardiac monitors or devices to determine the administration or discontinuation of DOACs based on the presence or absence of AF have demonstrated a reduction in DOAC use by 74.6% to 94% [7, 8], suggesting that current practices unnecessarily increase bleeding risk and healthcare costs. Implantable cardiac monitors and devices are invasive, and only the remote monitoring provider has information about AF onset, causing delays in DOAC administration. Recently, non‐invasive devices capable of continuous monitoring, heart rate analysis, and ECG functions have been developed. These devices alert users to abnormal heartbeats in real time, allowing for immediate action. We have chosen to use one of these devices, the Apple Watch, to investigate the efficacy and safety of Apple Watch‐guided personalized anticoagulation therapy.

## METHODS

2

### Objective

2.1

In patients who maintain sinus rhythm following ablation for AF, we will investigate whether Apple Watch‐guided personalized anticoagulation therapy—where DOACs are continued or discontinued based on the presence or absence of AF as monitored by the Apple Watch—will reduce DOAC usage compared to the conventional method of continuous anticoagulation.

### Study design

2.2

The study design is a multicenter, prospective, single‐arm intervention study. After confirming that the study patients meet the inclusion and exclusion criteria, consent will be obtained, and cases will be enrolled via the case registration system. After enrollment, the patients will wear an Apple Watch and begin monitoring for AF **(**Figure 1
**)**.

**FIGURE 1 joa313194-fig-0001:**
[figure not shown]
Study design. The red line indicates continuation of DOACs, the blue line indicates discontinuation of DOACs, the solid line indicates continuation of monitoring by the Apple Watch, and the dashed line indicates the discontinuation of monitoring by the Apple Watch. Heartbeat notification is defined as high heart rate notification and irregular heartbeat notification. AF, atrial fibrillation; DOAC, direct oral anticoagulant; ECG, electrocardiogram.

If no AF occurs for the first 30 days of monitoring, anticoagulants will be discontinued on day 31. AF is defined as the notification of irregular heartbeats and a high heart rate indicated by the Apple Watch, and AF, atrial flutter, and atrial tachycardia indicated by 12‐lead ECG or Holter ECG.

If AF is detected on the Apple Watch by day 30, the patient will obtain an ECG with the Apple Watch. Monitoring with the Apple Watch will then be discontinued. Thereafter the patient will see a physician within 7 days, and the physician will evaluate the ECG obtained by the patient with the Apple Watch. If the physician determines that the patient is not in AF, monitoring with the Apple Watch will be resumed. If the physician confirms that the patient is in AF, DOAC administration will be continued until the end of observation period.

If AF is detected on the Apple Watch after day 31, the patient will obtain an ECG with the Apple Watch. Monitoring by the Apple Watch will then be discontinued. At the same time, DOAC administration will be resumed. Thereafter, the patient will see a physician within 7 days, and the physician will evaluate the ECG obtained by the patient with the Apple Watch. If the physician determines that the patient is not in AF, DOAC administration will be discontinued and monitoring by the Apple Watch will be resumed. If the physician confirms that the patient is in AF, DOAC administration will be continued until the end of observation period.

If AF is confirmed by various ECG tests without notification from the Apple Watch, such as voluntary ECG recording by the ECG application on the Apple Watch or ECG tests at hospitals, the subject will be examined by a physician and, if determined to be in AF, will continue or resume taking DOACs and terminate the monitoring via the Apple Watch.

This study has been registered at the Japan Registry of Clinical Trials (jRCTs052230070) and adheres to the principles of the Declaration of Helsinki. The study protocol and informed consent forms have been reviewed and approved as a specific clinical trial in accordance with Clinical Trials Act by a certified review board (CRB), the Osaka University Clinical Research Review Committee (CRB5180007). All patients must provide informed written consent prior to participation in this study.

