### Apple Watch setting

2.3

Apple Watches from series 4 or later were used in this study. The Apple Watch can record heart rate using photoplethysmography and notify users when the heart rate is high, low, or irregular. High heart rate notification will be set to 120 bpm, and low heart rate notification will be disabled. The irregular rhythm notification will be enabled. The irregular rhythm notification can diagnose AF with a sensitivity of 78.9% and any arrhythmia, including AF, with a sensitivity of 98.2% [9]. ECG application implemented on the Apple Watch can diagnose AF with a sensitivity of 98.5% and specificity of 99.3% [9]. Both the irregular rhythm notification and ECG application are approved as medical devices by the Pharmaceuticals and Medical Devices Agency in Japan.

The Apple Watch needs to be recharged, and it will be recommended to allocate bath time for charging. It will be recommended to wear the watch even when sleeping, except during charging time.

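### After day 31, AF on a voluntary home watch ECG waits for a physician before DOACs restart, whereas a watch notification restarts them at once

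*Protocol article*

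**What the plan says.** All of the rules are in section 2.2 (Study design) of the protocol article.

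- **What counts as detection on the watch.** "AF is defined as the notification of irregular heartbeats and a high heart rate indicated by the Apple Watch"; the other route in the definition is a 12-lead or Holter ECG. A watch ECG is not part of the definition.
- **Notification after day 31.** The patient records a watch ECG and watch monitoring stops. Then: "At the same time, DOAC administration will be resumed. Thereafter, the patient will see a physician within 7 days". The restart does not depend on what the watch ECG shows. If the physician rules out AF, "DOAC administration will be discontinued and monitoring by the Apple Watch will be resumed". If AF is confirmed, DOACs stay on to the end of observation.
- **No notification.** "If AF is confirmed by various ECG tests without notification from the Apple Watch, such as voluntary ECG recording by the ECG application" or a hospital ECG, then "the subject will be examined by a physician and, if determined to be in AF, will continue or resume taking DOACs", and watch monitoring ends.

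Section 2.3 gives the accuracy of the two watch functions. For the notification: "The irregular rhythm notification can diagnose AF with a sensitivity of 78.9% and any arrhythmia, including AF, with a sensitivity of 98.2" per cent. The ECG application "can diagnose AF with a sensitivity of 98.5% and specificity of 99.3" per cent.

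**The concern.** A patient at home, off anticoagulation, who records a watch ECG that indicates AF is told to be examined before restarting. A patient with a notification restarts immediately, even if the accompanying ECG looks normal. A positive result from the ECG application, for which the article reports high sensitivity and specificity, therefore gets the slower response.

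This sits badly with the reason for the strategy. The Introduction argues that "DOACs can be administered upon the onset of AF" and faults implantable monitors for delaying treatment.

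The situation is foreseeable. Section 2.2 provides for it, the stated sensitivity of the notification for AF is well below 100%, and section 4 says that the watch does not notify during exercise and must come off for charging.

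What is at stake is a period of AF without anticoagulation in a patient who already has evidence of AF in hand.

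**Working it through.** **1. The two pathways after day 31, side by side (section 2.2)**

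| Step | Notification | Voluntary watch ECG, no notification |
|---|---|---|
| Trigger | Watch notification | Watch ECG indicating AF |
| DOAC restart | At once | After physician's determination of AF |
| Time limit for physician | 7 days | None stated |
| Reversal if not AF | DOACs stopped, monitoring restarted | Not needed, since nothing was restarted |

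The second column fixes an order of actions. The sentence also covers hospital ECGs, but there a physician is likely to be at hand and the delay may be nil, so the point is confined to home recordings.

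**2. How often it could arise**

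Share of AF not flagged by the irregular rhythm notification: 100 − 78.9 = 21.1%. This cannot be turned into a number of patients. Section 2.3 does not say whether the sensitivity is per episode or per patient. The share caught by the 120 bpm alert, the AF recurrence rate after day 31 and the use of voluntary ECGs are not given. The 98.2% figure concerns any arrhythmia, so it does not bound the share of AF missed.

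**3. Embolic risk during the wait**

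Assumed wait: 0 days (same-day examination) to 7 days (the limit in the notified pathway, borrowed because this pathway has none). Section 3 gives 0.03% to 0.6% per year without anticoagulation after ablation.

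- Lower: 0.03% × 7/365 = 0.0006%
- Upper: 0.6% × 7/365 = 0.012%

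These are average rates, not rates during AF, so they show scale only.

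**4. Effect on the primary endpoint**

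Section 2.6 counts DOAC days over person-days from day 31 to day 360, which is 330 days per patient. Assuming full follow-up of 50 patients: 50 × 330 = 16,500 person-days. One patient waiting 7 days: 7/16,500 = 0.04 percentage points.

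**5. Cost of an immediate restart**

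The illustration is 100 voluntary recordings in sinus rhythm, at the stated specificity of 99.3%.

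- False positives: 100 × (1 − 0.993) = 0.7
- DOAC days, at up to 7 days each: 0.7 × 7 = 4.9
- Share of person-days: 4.9/16,500 = 0.03 percentage points

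The count would be higher if patients also acted on inconclusive tracings.

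**The case against.** **The article is condensed, and the paragraph is a catch-all.** It covers both periods and every ECG source, and interim instructions may be in the full protocol or in Figure 1, neither of which is shown. That possibility stands. But the printed sentence does more than stay silent: it makes resumption conditional on a physician's determination, directly after a paragraph that restarts DOACs without one. If the full protocol already provides an interim restart, only the article's sentence needs correcting.

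**The trigger speaks of confirmed AF, which may mean a clinician has already read the tracing.** This is possible, but examination and determination are still placed before resumption.

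**The choice is defensible.** Voluntary ECGs can be repeated without limit, so asking for a physician's view first is not unreasonable. Entry is limited to a CHA2DS2-VASc score of 3 or less without previous cerebral infarction. The Discussion cites a study finding no excess of embolic events with subclinical AF under 24 hours, and meta-analyses in which stopping anticoagulation did not change embolic risk. The line in the Introduction contrasts DOACs with warfarin and is not a timing rule. All of this stands and limits the size of the point. It does not explain why a notification alone earns the faster restart.

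**Stronger readings to avoid.** A reader might infer that about a fifth of AF recurrences will go untreated while patients wait. The document does not support that: persisting AF may trigger a later notification, the 120 bpm alert may catch some cases, and only patients who record a voluntary ECG enter this pathway. Nor does the document show that the notification is the less specific signal, because no specificity is given for it.

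**Conclusion.** The point holds as a limited inconsistency in a stated rule. After day 31, a voluntary home watch ECG indicating AF leads to later resumption of DOACs than a notification does, with neither an interim restart nor a deadline, and the accuracy figures in section 2.3 give no reason for the difference.

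The absolute risk is probably very small. On the Discussion's evidence, a wait matters mainly if it exceeds a day and AF persists. The primary endpoint is essentially unaffected, so a claim that the rule biases the trial's main result would not be supported. The size rests on an assumed wait of 0 to 7 days, average embolic rates, and full follow-up of 50 patients. The number of patients affected is unknown. The case for change is consistency and patient safety at low cost.

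**What to change.** Split the last paragraph on detection in section 2.2 so that voluntary home watch ECGs follow the notified pathway. Suggested wording:

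*After day 31, a patient whose voluntary watch ECG suggests AF with no preceding notification stops watch monitoring, restarts the DOAC straight away and attends a physician within 7 days. Where the physician rules out AF, the DOAC is stopped and watch monitoring restarts. Where AF is confirmed, the DOAC is kept on for the rest of the observation period.*

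Leave the rule for hospital ECGs unchanged.

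The clinical cost is the small number of extra DOAC days worked out above, reversible at the visit. The administrative cost is one amended paragraph, a notice to the 9 sites and to patients, and probably an amendment through the certified review board, since a drug-restart rule changes. Enrollment closed in April 2024 and the last follow-up is due in April 2025, so the change helps only patients still in follow-up and later trials that reuse this strategy.

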### Apple Watch setting

2.3

Apple Watches from series 4 or later were used in this study. The Apple Watch can record heart rate using photoplethysmography and notify users when the heart rate is high, low, or irregular. High heart rate notification will be set to 120 bpm, and low heart rate notification will be disabled. The irregular rhythm notification will be enabled. The irregular rhythm notification can diagnose AF with a sensitivity of 78.9% and any arrhythmia, including AF, with a sensitivity of 98.2% [9]. ECG application implemented on the Apple Watch can diagnose AF with a sensitivity of 98.5% and specificity of 99.3% [9]. Both the irregular rhythm notification and ECG application are approved as medical devices by the Pharmaceuticals and Medical Devices Agency in Japan.

The Apple Watch needs to be recharged, and it will be recommended to allocate bath time for charging. It will be recommended to wear the watch even when sleeping, except during charging time.

### Eligibility criteria

2.4

The study population will consist of patients who maintain sinus rhythm after ablation for AF and are taking DOACs. Inclusion and exclusion criteria are summarized in Table 1. A signed informed consent form approved by CRB will be obtained from each patient prior to any intervention.

**TABLE 1 joa313194-tbl-0001:** Eligibility criteria.

**Inclusion criteria**
No AF recurrence after 3 months following catheter ablation
Patients using DOACs
Patients using an iPhone (version 8 or later, SE second generation or later)
CHA_2_DS_2_‐VASc score of 3 or less
Age 22 years or older
Patients who can provide written consent
**Exclusion criteria**
Mechanical valve
Severe mitral stenosis
Cases in which anticoagulation is essential (deep venous thrombosis, intracardiac thrombus, etc.)
Resting heart rate of 100 beats/min or higher
Pacemaker implantation
Patients with a history of fatal arrhythmia (ventricular tachycardia, ventricular fibrillation) or with an implantable cardioverter defibrillator (ICD)
Post‐operative heart transplantation
Chronic hemodialysis
Patients with a history of cerebral infarction
Patients scheduled for elective surgery during the observation period, including catheterization
Patients who have difficulty operating the device due to visual impairment, cognitive impairment, etc.
Other subjects deemed inappropriate by the investigators

### Data collection and follow‐up

2.5

At the time of informed consent, baseline data, medical history, comorbidities, medications, blood test, 12‐lead ECG, transthoracic echocardiogram, date of catheter ablation for AF, and type of AF prior to ablation will be collected. After the enrollment, patients will continue to wear the Apple Watch until the end of the observation period, 12 months after enrollment. Patients will be strongly encouraged to wear the Apple Watch even while sleeping.

Patients will be followed at 1, 3, 6, 9, and 12 months after enrolment. A 12‐lead ECG, alerts, and ECG of the Apple Watch, number of days wearing the Apple Watch, and DOAC medication status will be obtained at each follow‐up visit. Medication assessment will be performed at 12 months. Symptom‐driven 12‐lead ECG, Holter ECG, and any other devices capable of obtaining ECGs can be used at any time at the physician's discretion. Outcomes, adverse events, and malfunctions of the Apple Watch will be collected whenever they occur during the observation period.

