### Study endpoints

2.6

The primary endpoint of this study will be the percentage reduction in the total number of days with DOACs from day 31 to day 360 compared to the conventional method of continuous anticoagulation. Analysis of the primary endpoint will be calculated as follows: the denominator will be the observation period (person‐days) and the numerator will be the total number of days with DOACs during the observation period. The degree of decrease will be evaluated by calculating “1 ‐ the rate of DOAC use during the observation period”. The observation period used in this calculation will be from day 31 to day 360. For DOACs taken twice a day, if taken only in the morning or evening, the days with DOACs will be counted as 0.5 days.

The secondary endpoints will include all‐cause death, stroke, systemic thromboembolism, bleeding events, and malfunctions of the Apple Watch. Bleeding events will be defined as major bleeding according to the ISTH bleeding criteria [10] and any overt bleeding events other than the major bleeding. Stroke will be defined as a non‐traumatic focal neurologic deficit lasting more than 24 hours, diagnosed by brain imaging or autopsy as ischemic stroke [11]. Systemic thromboembolism will be defined as a clinical history consistent with acute loss of peripheral blood flow and findings of embolism through objective testing such as imaging studies and surgical specimens.

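### The primary endpoint credits days when a DOAC was due but not taken as reduction, so failures of the restart step improve the result

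*Protocol article*

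**What the plan says.** Protocol article, section 2.6 (Study endpoints), defines the primary result. The denominator is person-days, and "the numerator will be the total number of days with DOACs during the observation period". The reported quantity is "1 ‐ the rate of DOAC use during the observation period". On the window it says: "The observation period used in this calculation will be from day 31 to day 360". For twice-daily drugs, "if taken only in the morning or evening, the days with DOACs will be counted as 0.5 days".

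Section 2.2 (Study design) says when a DOAC is due in that window. After an alert the patient records a watch ECG, resumes the DOAC at once and sees a physician within 7 days. If the physician rules AF out, the DOAC is stopped again. If AF is confirmed, it continues for the rest of the observation period. AF found without an alert also leads to a physician's examination and, if confirmed, to resumption.

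Section 2.5 (Data collection and follow-up) gives the schedule: "Patients will be followed at 1, 3, 6, 9, and 12 months after enrolment". At each of these visits the watch alerts and watch ECGs are obtained, and "DOAC medication status will be obtained at each" follow-up visit. It adds: "Medication assessment will be performed at 12 months". The content of that assessment is not described.

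**The concern.** The formula counts days with a DOAC taken and treats every other day as reduction. It does not ask why the DOAC was not taken. Two kinds of day are pooled:

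- days off DOAC because the strategy directs it (no alert and no AF), which is the saving the trial wants to show;
- days when section 2.2 calls for a DOAC but the patient started late, never started, or missed doses after starting.

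The second kind is a failure of the strategy, yet it moves the primary result in the favourable direction. The trial therefore cannot tell from its primary figure whether the watch-guided restart worked.

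This matters for the rationale too. The Introduction faults implantable monitors for "causing delays in DOAC administration" and presents the watch as allowing immediate action. No endpoint in section 2.6 measures the time from alert to first dose, although alerts are already collected.

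**Working it through.** **Inputs.** Window: 360 − 31 + 1 = 330 days (section 2.6). Analysed patients: 54 − 4 = 50, which agrees with section 2.10. The sample size is resource-based (section 2.8), so there is no power calculation to reproduce. Person-days, if all 50 complete the window: 50 × 330 = 16,500. The documents give neither the number of restarts nor adherence, so those values below are assumptions.

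**Formula.** Reduction = 1 − (DOAC days taken / 16,500). A shortfall of d days raises the result by 100 × d / 16,500 points.

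**Weight of single errors.**

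- Half a day: 0.5 / 16,500 = 0.003 points.
- One restart late or misdated by 7 days: 7 / 16,500 = 0.04 points. If all err in the same direction, 10 restarts give 70 / 16,500 = 0.42 points and 20 give 140 / 16,500 = 0.85 points.
- One alert overlooked until the next scheduled visit: the longest gap is three months, about 91 days, so up to 91 / 16,500 = 0.55 points. If alerts fall evenly within the gap, the average is half of that: 45.5 / 16,500 = 0.28 points.

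**Effect of restart failure on the result.** Assume k of 50 patients should restart at times spread evenly over the window and stay on DOAC to day 360, a mean of 330 / 2 = 165 days each. DOAC days due are 165k: 1,650 for k = 10 and 3,300 for k = 20.

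| Behaviour | k = 10 | k = 20 |
|---|---|---|
| All due days taken | 1 − 1,650/16,500 = 90.0% | 1 − 3,300/16,500 = 80.0% |
| 10% of due days missed after restart | 1 − 1,485/16,500 = 91.0% | 1 − 2,970/16,500 = 82.0% |
| 20% of restarts missed entirely | 1 − 1,320/16,500 = 92.0% | 1 − 2,640/16,500 = 84.0% |
| No restarts at all | 100% | 100% |

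The score rises with every step away from the strategy.

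**Counting due-but-not-taken days as DOAC days.** Use 1 − (taken + due-but-not-taken) / 16,500. For k = 10 with 20% of restarts missed: 1 − (1,320 + 330) / 16,500 = 90.0%, against 92.0% under the stated formula. The 2.0-point gap between the two figures is the part of the apparent reduction that comes from restart failure.

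**The case against.** **The endpoint measures what it says.** It is defined on days actually taken, so a day with no dose is correctly a DOAC-free day. Whether it should count as a saving is a question about the estimand, and better recording alone would not remove it. This stands, and it is why the fix keeps the formula and adds a second figure.

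**The schedule is better than it looks.** A reader might infer from section 2.5 that intake is dated by recall alone, so that a restart in month 4 is first recorded at month 6. The document does not support this. It names no source for the daily counts, but a condensed article may leave diaries or tablet counts to the full protocol, and the morning/evening rule suggests that dose-level recording was intended. The physician visit within 7 days also gives an anchor well before the next scheduled visit. Where the pathway is followed, dating error is about 7 days at most.

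**Recording error is not one-sided.** A restart can be dated too early or too late, and patients may over-report doses, which would lower the reported reduction. The upward direction belongs to doses that were truly missed and to late or absent restarts, not to misdating.

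**The effect is small.** One overlooked alert is worth at most 0.55 points, against reductions of 74.6% to 94% in the studies cited in the Introduction. That is fair for isolated events. But the 7-day visit depends on the patient noticing the alert: an overlooked alert produces neither a restart nor a visit, and the next alert review that the article describes is the scheduled one. Nor does the 7-day visit capture doses missed later.

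**Conclusion.** The concern holds as a flaw in how the primary result is scored. By its stated formula, days when a DOAC was due but not taken are credited as reduction, and a complete failure to restart would score 100%. This follows from sections 2.2 and 2.6 however intake is recorded.

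The likely size is modest and cannot be computed from the document. Under the assumptions of 10 or 20 restarts, missing a fifth of them adds 2.0 or 4.0 points, and missing 10% of due days after restart adds 1.0 or 2.0 points. These rest on evenly spread restart times, full follow-up and confirmed AF in every restart.

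The wider claim, that the schedule cannot support the endpoint's half-day counting, is not established. A half-day carries 0.003 points, and the sources of the counts may be set out in the full protocol.

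**What to change.** 1. Keep the stated formula as the primary result.
2. Before analysis, classify each off-DOAC day in days 31 to 360 as protocol-directed or due-but-not-taken. Take the definition of a due day from section 2.2 as it stands: from an alert to the physician's decision, and from confirmation of AF to the end of the window. For an overlooked alert, state in advance that days from the alert to its review count as due. Use the alerts and DOAC status already collected at each visit, and the 7-day review.
3. Report both totals, and show the primary percentage a second time with due-but-not-taken days not credited as reduction.
4. Report the alert-to-first-dose interval, including alerts with no restart.
5. For remaining follow-up, record DOAC start and stop dates at the alert review and at each scheduled visit, rather than relying on the 12-month assessment. State the source of the daily counts.

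The cost is slight extra data work and a possibly less favourable second figure. Treatment, visits and sample size do not change. Enrolment is complete, so item 5 cannot recover elapsed days; for those, items 2 to 4 depend on the alert and intake data already held.
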